**Methods:**

A prospective, two-arm, single-blinded, randomized controlled trial will be conducted with an estimated sample size of 100 CLBP patients, assigned to either the MultiMove group or a control group. The intervention group will receive MultiMove twice a week for 60 min each over a period of 12 weeks. The primary outcome will be the mobility and function of the lower extremities assessed by the Timed Up-and-Go Test. Secondary outcomes comprise further physical and physiological functions (e.g. gait variability and haemodynamic response in the prefrontal cortex during motor-cognitive dual tasks), subjective health state (e.g. disability in daily life), executive functions (e.g. cognitive flexibility) and psychosocial aspects (e.g. kinesiophobia). Measures will be taken at baseline, after the intervention and at a 12-week follow-up. It is assumed that MultiMove improves the mentioned outcome parameters.

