### Primary objective

To test the effect of MultiMove on CLBP patients’ physical function (TUG performance) relative to the conventional conservative therapy.

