## Methods

### Study design and setting

The current study is designed as a prospective, two-arm randomized, controlled, superiority clinical trial. To assess the effect of MultiMove on the measures presented above in CLBP patients, subjects will be allocated to an intervention group (IG) or a control group (CG) using block randomization (1:1 allocation) [47]. The primary and secondary outcomes will be assessed at three time points (see Fig. 1, a detailed overview of the outcome measures can be found in Table 3).

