### Sample size

Sample size was calculated using G*Power (version 3.1.9.7.). Because previous studies have shown large effect sizes for changes in the TUG performance after single interventions (dancing [49], strength training [50]) as well as after multimodal interventions [51] in healthy older adults, a large effect size (f = 0.40) was assumed for the sample size calculation. Considering an α level of 0.05, a power of 0.95, two groups and two covariates (baseline scores and, when required, e.g. age, sex, etc.), the required total sample size for an analysis of covariance (ANCOVA) amounted 84 participants. With a hypothesized dropout rate of around 15%, a total sample size of 100 participants seems to be legitimated.

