### Data analysis and management

Data will be analysed using IBM SPSS 26.0 (SPSS Inc., Chicago, IL). At first, a descriptive analysis will be conducted to identify outliers, distributions and to display the baseline characteristics of both groups (means, proportions, standard deviations). To evaluate the effects of the intervention, data of all patients will be processed, regardless of whether they fully received or dropped out of the intervention (intention-to-treat-analysis). Thereby, data will be analysed until the date of drop out. As a secondary analysis, only the data from the participants who participated at least 80% of the intervention will be included in a per-protocol analysis. Missing data will be imputed using multiple imputation, under the assumption that data are missing at random. Statistical significance level will be set at *p* ≤ 0.05 (1-sided).

In order to analyse differences between the groups at the time points post and follow-up, two ANCOVAs with baseline adjustments will be undertaken (covariates: baseline values and, when required, e.g. age, sex etc.) for all outcome measures. Subsequently, alpha-adjustments will be undertaken. In case the assumptions for the ANCOVA will be violated, mixed models will be used. To further elaborate the outcomes and their interactions, additional parametric or nonparametric statistical analyses will be applied. Exploratory mediation analysis will be performed supplementary.

To preserve the confidentiality, all participants will receive a specific code with which the data will be labelled, while the participants contact data will remain under lock. The collected data will be stored digitally and can only be accessed by the study group. Therefore, the data will be transmitted by one person and checked for correctness by another (transmission errors and plausibility). In this study, no data monitoring committee and interim analysis will be established, because of the minimal risks associated with the intervention. Overall, the data management will be in line with of the European General Data Protection Regulation.

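### The sample size gives 0.95 power for one TUG comparison at full alpha, but the analysis tests TUG at two time points and adjusts alpha without naming a primary test, so 0.95 is not assured

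*Protocol article*

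**What the plan says.** TUG is clearly the only primary outcome. The abstract states it ("The primary outcome will be the mobility and function of the lower extremities assessed by the Timed Up-and-Go Test"), and the primary objective is "To test the effect of MultiMove on CLBP patients’ physical function (TUG performance) relative to the conventional conservative therapy". Neither gives a time point. The study design section adds that "The primary and secondary outcomes will be assessed at three time points", namely baseline, post (t1) and follow-up (t2).

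Under Sample size, "a large effect size (f = 0.40) was assumed for the sample size calculation". The calculation continues: "Considering an α level of 0.05, a power of 0.95, two groups and two covariates", and "the required total sample size for an analysis of covariance (ANCOVA) amounted 84 participants". An allowance of about 15% for dropout brings the total to 100. No adjustment for multiple tests enters.

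Under Data analysis and management: "In order to analyse differences between the groups at the time points post and follow-up, two ANCOVAs with baseline adjustments will be undertaken". This applies "for all outcome measures. Subsequently, alpha-adjustments will be undertaken". The same section sets the significance level at 0.05, one-sided. It does not say which tests the adjustment covers or how it is done, and it does not exempt TUG.

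**The concern.** The two sections describe different tests. The sample size assumes one TUG comparison with the whole of alpha. The analysis plans two TUG comparisons, followed by an adjustment whose scope is left open. Taken as written, the adjustment sentence follows directly on a sentence about every outcome, so the primary test may receive only a share of alpha.

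Two things are at stake. First, 0.95 is the article's justification for recruiting 100 people, and it may not be the power of the test that decides the trial. Second, with no primary time point fixed, a reader of the results cannot tell which TUG comparison, or which combination of the two, was meant to answer the primary objective.

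**Working it through.** **Inputs.** From Sample size: f = 0.40, α = 0.05, power 0.95, two groups, two covariates, N = 84, dropout about 15%. From Data analysis and management: two time points per outcome, one-sided 0.05, adjustment method and family not stated. Assumption: Bonferroni, α/m for m tests.

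**Formula.** ANCOVA F test with df1 = 1, df2 = N − 2 groups − 2 covariates, and noncentrality λ = f²N. Power = P(F′ > critical F at α/m). For a one-sided test, the noncentral t with the same df2 and δ = f√N.

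**Step 1: reproduce the plan's figure.** At N = 84, df2 = 80 and λ = 0.16 × 84 = 13.44. The critical F at 0.05 is 3.96, and power is 0.952. N = 83 gives 0.949, so 84 is the smallest N that reaches 0.95. The dropout step also reproduces: 84 / 0.85 = 98.8, so 99, rounded up to 100. The 84 therefore belongs to one unadjusted, non-directional test. A one-sided 0.05 test would have needed only 70.

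**Step 2: power of one TUG test at N = 84 after adjustment.** Here δ = √13.44 = 3.67.

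| Tests sharing alpha | α/m | Two-sided power (critical F) | One-sided power (critical t) |
|---|---|---|---|
| 1 (as sized) | 0.05 | 0.952 (3.96) | 0.977 (1.66) |
| 2 (TUG at t1 and t2) | 0.025 | 0.914 (5.22) | 0.952 (1.99) |
| 22 (illustration) | 0.00227 | 0.694 (9.94) | 0.769 (2.92) |

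The 22 comes from the 11 outcome instruments in Table 3 (four physical, two subjective health, one dual-task, two executive function, two psychosocial), with one parameter each, at two times: 11 × 2 = 22. Several instruments yield more than one parameter, so the count could be higher. Holm or an ordered procedure would lose less power than Bonferroni.

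**Step 3: evaluable N for 0.95.** Two tests: 98 two-sided, 84 one-sided. Twenty-two tests: 143 two-sided, 130 one-sided.

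**Step 4: why the one-sided, two-test figure matches the plan.** One-sided 0.05 halved is 0.025 in one tail, which is the same threshold as the two-sided 0.05 used for sizing. That is why 0.952 reappears.

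**The case against.** The best defence has four parts.

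- **The family is not stated.** TUG is set apart as sole primary outcome in the abstract, the objectives, the Table 3 footnote and its own section. Adjusting over the two TUG tests alone fits the text as well as pooling with everything. This stands. A reader might infer that the plan drops power to about 0.69, but that needs Bonferroni, a count of 22 and full pooling, none of which the article states.
- **The narrow reading may lose nothing.** At the article's own one-sided 0.05, split over two TUG tests, power is 0.952. If success means either TUG test being significant, two-sided power at 0.025 each is about 0.94 to 0.97 (simulation, assuming f = 0.40 at both times and correlation 0.9 down to 0.5). If all 100 participants contribute full information through imputation, the two-sided per-test figure is 0.956, which is an upper bound. This also stands, but each version depends on a choice the article does not make.
- **False positives.** A reader might infer that two chances on TUG inflate the type I error. The documents do not support this, because the article says alpha will be adjusted. If the adjustment covers both TUG tests, an either-or claim is controlled.
- **This is detail for an analysis plan.** The adjustment method may well be. But the article itself states the two tests, the adjustment and the power, and these do not fit together. The time point of the primary comparison is also part of the primary question.

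The text leans towards t1, since the effect size rests on TUG changes after interventions, but it never says so.

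**Conclusion.** The point holds in a limited form. The stated 0.95 belongs to one TUG test at the full alpha of 0.05. The analysis section plans two TUG tests with an adjustment of unstated scope and names neither as primary. The stated power is therefore not assured for the primary test; it is not shown to be lost.

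The size depends on the reading. With alpha split over the two TUG tests only, per-test power is 0.914 two-sided or 0.952 one-sided, so the shortfall is small or nil. With TUG pooled with all outcomes it is about 0.69 or 0.77, as an illustration only. All figures assume f = 0.40, 84 evaluable participants and Bonferroni. The finding that the primary time point and the adjustment family are not fixed needs none of these assumptions.

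The analysis is one-sided while the 84 reproduces only as a non-directional test. That mismatch is a separate matter, to be reconciled on its own.

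**What to change.** In Data analysis and management, and in the primary objective:

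1. Name the between-group TUG difference at one time point as the single confirmatory test, at the alpha used in the sample size calculation. t1, directly after the intervention, fits the basis of the assumed effect size.
2. Test TUG at the other time point next, only if the first is significant. This fixed sequence costs no alpha.
3. State that the alpha adjustment applies to the secondary outcomes only, and say which of them form the family.

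The stated power of 0.95 at N = 84 then belongs to the planned primary test. An equally valid alternative is to keep both TUG tests as co-candidates with a split alpha, and to size the trial for that: 98 evaluable two-sided under Bonferroni, or 98 / 0.85 = 115.3, so 116 recruited.

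The first route needs a few lines of text, settled before any outcome data are compared by group, and no extra participants or measurements. Its cost is that a TUG effect appearing only at t2 could not be claimed as confirmatory.

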## Discussion

To the best of our knowledge, MultiMove is the first study combining motor-cognitive with dance-therapeutic as well as strength and flexibility training to address the multifaceted impairments of CLBP. First of all, it is expected that the combination of these three components will stimulate the participants in moving their spine constantly and therefore counteract the fear of moving. The group-setting will additionally provide the opportunity to experience mutual support and encouragement from peers in the engagement for physical activities [38].

Furthermore, the hypothesised advantage of MultiMove for CLBP patients is seen in the intertwining effects of the three training components. The basic component with its specific strengthening and flexibility exercises targets the whole lumbar spine including the lumbar multifidus and transversus abdominus muscles, which are known to promote the pain situation in CLPB patients [86]. The assumed enhanced lumbar stability could counteract the degeneration processes of the vertebrae and joint structures and therefore build the foundation for functional performances required during everyday activities and addressed in the motor-cognitive and dance-therapeutic component of MultiMove. Moreover, most of the movements performed in daily life are accompanied by a second task (e.g. walking and talking). This aspect will be targeted during the motor-cognitive training, where the patients will be confronted with constantly novel exercises requiring interactions between cognitive and physical performance. This ability, learned in a playful setting, might be especially valuable in enhancing the dual task performance of the patients. The following dance-therapeutic intervention stresses the mentioned aspects, as it addresses the trunk range of motion and incorporates cognitive tasks. Although, it has been shown that a dancing program is suitable to improve the motor-cognitive dual task capability in elderly [41], this study did not investigate brain activity during dual task walking. Consequently, a major advantage of this study can be seen in the methodological approach. Due to the combination of neuropsychological tests, gait analysis and fNIRS, a detailed elaboration of the respective influences on the motor-cognitive performance will be possible. These results will contribute to a better understanding which of these entities have to be addressed to reduce the impairments of CLBP patients. Furthermore, the randomized controlled design with the additional follow-up measurement will enable high level evidence on the long-term effects of MultiMove. Finally, due to the aspect that MultiMove does not need special requirements, it could be delivered on low cost in all areas, where it is needed.

One limitation in the application of MultiMove is that the participants must be physically able to participate actively in the intervention over 60 min. Hence, CLBP patients with severe physical impairments cannot be included.

The presented study is only the first stage of a three staged project. In the second stage, it is intended to test an adapted multimodal treatment during inpatient rehabilitation and in the third stage, the programme will be integrated into the medical prevention. The overall objective is to establish the multimodal treatment into cross-sectoral care to sustainably improve the situation of CLBP patients along the entire medical supply chain.

## Data Availability

Not applicable.

## Abbreviations

BDI-II: Beck Depression Inventory II
CES: Closed eyes standing
CG: Control group
CLBP: Chronic low back pain
CSQ-D: Coping Strategies Questionnaire – German Version
DSL: Double step length
DTS: Dual task standing
DTW: Dual task walking
FRSTST: Five-repetition sit-to-stand test
fNIRS: Functional near-infrared spectroscopy
ICD-10: International Classification of Diseases 10th revision
IG: Intervention group
IMUs: Inertial measurement units
IRB: Institutional review board
LBP: Low back pain
MTC: Minimum toe clearance
MultiMove: Multimodal intervention
NRS: Numerical rating scale
ODI: Oswestry Disability Index
OvGU: Otto von Guericke University
POMS-F: Profile of Mood States- fatigue subscale
PFC: Prefrontal cortex
STW: Single task walking
TMT: Trail Making Test
TSK-GV: Tampa Scale of Kinesiophobia – German Version
TUG: Timed Up-and-Go
6MWT: 6-min walk test
